## 7.0 PROCEDURE FOR COLLECTION, TESTING AND STORAGE OF BLOOD SAMPLES

### Purpose

To perform the following laboratory work:

- HIV serology
- Syphilis serology
- Hemoglobin measurement
- Archive plasma

### When

At enrollment and subsequent visits.

### By whom

Project nurses.

## 7.4 Supplies needed

1. Lancets
2. 5 or 7mm needle
3. 5 ml Red-top collection vacutainer
4. 10 ml Purple-top collection vacutainers
5. Hemocuvettes
6. Alcohol swabs

### Description of procedures

1. For rapid HIV testing, blood is collected from a finger prick (or infant cord blood for late presenters in the NVAZ study). A study nurse will use a drop of whole blood on a rapid HIV test kit to immediately determine if a specimen is HIV positive or negative based on the manufacturer's instructions.
2. Specimens positive on a rapid HIV test are confirmed by conventional ELISA (e.g., Wellcozyme HIV test) using serum samples according to manufacturer's instructions. If a specimen is borderline, a Western blot test will be conducted to confirm ELISA results.
3. Women who are HIV tested for the first time will be tested using two separate conventional ELISA tests.
3. All HIV negative women who seroconvert during the METRO Study will be confirmed by a WB test according to manufacturer's instructions.
4. Hemoglobin is estimated on a drop of blood (collected on a hemocuvette) using a Hemocue machine. The hemoglobin results are read immediately by a project nurse.

5. Syphilis serology (RPR and TPHA) will be performed on sera collected from all participants according to manufacturers' specifications. TPHA confirmatory tests will be performed only on RPR positive samples.
6. Two aliquots of approximately 1.5 ml plasma will be archived. Only plasma will be archived - not serum.

7.6 Processing and storage

1. HIV ELISA analysis on maternal blood samples will be performed at the JHP laboratory in Blantyre. Every effort will be made to make the results of the confirmatory tests available before the woman is discharged after delivery. Delayed results will be available by Day 7 visit postnatally.
2. Archived plasma will be stored in a -70°C freezer.

## 8.0 PROCEDURE FOR COLLECTION AND TESTING OF VAGINAL AND URINE SAMPLES

### 8.1 Purpose

To collect vaginal and urine samples to test, respectively, for bacterial vaginosis (and other genital infections; see section 3.2) and pregnancy.

### 8.2 When

At enrollment and subsequent visits.

### 8.3 By whom

By the project nurses.

### 8.4 Supplies needed

- pH strip
- Cotton-tipped applicator swabs
- Test tube containing sterile saline
- 10% KOH
- Glass slides
- Sterile centrifuge tubes for collection of cervico-vaginal fluid (CVL)
- Pregnancy test kit

### 8.5 Description of procedures

1. Vaginal pH. A pH strip is held face-down against the lateral wall of the vagina with a cotton tipped applicator until moistened with vaginal fluid. The pH is read by comparing the color on the strip to the reference colors provided by the manufacturer.
2. Vaginal wet mount. A cotton-tipped applicator is used to swab the lateral wall of the vagina and placed in a test tube containing 0.5 ml of sterile saline. The fluid is examined at the lab for presence of clue cells and motile trichomonads. A Whiff test is also done on this sample. A drop of the fluid is mixed with 10% KOH for detection of yeast cells (buds and hyphae).
3. Vaginal smears. A separate cotton-tipped applicator will be used to collect vaginal and cervical swabs to prepare a smear for Gram staining. The applicators are gently rolled (not rubbed) across the surface of the a glass slide to create a single layer of cells. The slides are allowed to air dry and stored. A separate protocol will be provided for Gram-staining, examination under oil immersion, and description of bacterial vaginosis morphology.
4. Archiving of cervico-vaginal swab. A cervico-vaginal swab sample will also be archived.
5. Urine pregnancy testing. Urine is tested for the presence of hCG for pregnancy diagnosis by a rapid dipstick analysis according to manufacturers' instructions.

## 9. GENERAL GUIDELINES FOR SHIPMENT OF SAMPLES

### When to ship

On request by [name].

### How to ship

Via DHL or other couriers, as appropriately arranged.

### Procedure

To ship frozen samples, dry shippers must be primed with liquid nitrogen for at least 48 hours prior to shipping. The shipment must leave on an appropriate day (e.g., Monday or Tuesday) to ensure the shippers arrive before the end of the working week in the U.S.

### Some important notes

- DO NOT stick the green sticker (indicating liquid nitrogen) on the shippers, since the actual shipper does not contain any liquid nitrogen anymore.

Each shipment should be accompanied by the following VALID papers:

- Department of Health & Human Services permit to import or transfer etiological agents or vectors of human disease, which MUST be in [name] name
- A PERMIT STICKER of the Department of Health & Human Services, with permit number stuck on the dry shipper

The value of the shipment is M.K. 50.00 (customs purposes) and contents must be specified as *potentially infectious human blood specimens* (according to the shipping permit's description of material).

[name] must be informed a head of time of:

- intended date of shipment
- airway bill number
- estimated date of arrival

When shipping, please keep in mind USA public holidays; Malawi public holidays; the size of the aircraft to Harare/S. Africa (when shipping two large dry shippers at the same time; it's best to phone the Courier beforehand to enquire if these shipments can fit in the aircraft).

Always leave appropriate contact numbers with the Courier so that they can call you if a problem is encountered.

## 10.0 STUDY FORMS AND DOCUMENTATION PROCEDURES

### 10.1.1 Study Forms (See Appendix 3)

#### **Mother's Study Forms**

##### Enrollment Forms:

1. Locator Information
2. Enrollment History (Demographics, Behaviour, and Genital History)
3. Physical Exam
4. Product Dispensation
5. Laboratory Check-list
6. Local Laboratory Results
7. Comments

##### Follow-up Forms:

1. Locator Information - update only
2. Follow-up Behaviour and Genital History
3. Acceptability History (complete at test of cure visits)
4. Physical Exam
5. Product Monitoring and Genital History (complete at test of cure visits)
6. Product Dispensation
7. Laboratory Check-list
8. Local Laboratory Results
9. Missed Visit
10. Adverse Experience
11. Concomitant Medication
12. Termination
13. Comments

### 10.1.2 Purpose of each study form

Most of the forms are self-explanatory. Only few will be explained here. The Locator Information Form is completed at time of enrollment of the woman and updated at each follow-up visit. This form will be used to trace women in situations where participants are late or miss a scheduled visit. Therefore, complete this form with extra care, so that it serves its purpose (i.e., to locate a study participant in a particular neighbourhood or township). If you do not do it well now, you will bear the difficulties later!!! The Comment Form is an open ended form which records additional information about a specific participant, or to clarify data recorded on another form. Information about unscheduled visits is also recorded on this form. If this is a scheduled visit, enter visit number on this form as usual (i.e., the current visit number). If this is an unscheduled visit, leave the visit number blank - only enter ID# and date of visit. Please write legibly on this form. The Missed Visit Form is completed when a participant has missed a scheduled visit. Enter on this form the visit # of the scheduled visit that was

missed. The Termination Form is completed whenever a participant terminates from the study. The termination date and the reason for termination (e.g., death of the mother) are entered.

10.1.3 By Whom

Study nurses.

10.1.4 Where/When

At QECH or participating clinics at the time indicated on each form.

10.1.5 Procedure

To complete these forms, follow carefully the instructions on each form. Write legibly using a black pen. Enter the responses in the boxes or lines provided. No scribbling is allowed. No wipe-outs. When a correction is made, make a neat single line crossing over the original entry; initial and date this correction and enter your code at the margin. Please follow these instructions carefully.

10.2 Clinic specific METRO study log-book

10.2.1 Purpose

To create an overall METRO study registry.

10.2.2 When

First contact of a woman (prior to enrollment) with hospital or a health center as a potential study client.

10.2.3 By whom

Study nurses.

10.2.4 Procedure

Each participating clinic will register women presenting postnatally in a designated METRO study log book. The log book will include pertinent information such as name, date and residence and any other information required at the start of the study.

10.3. Documentation procedures

The study site principal investigator will maintain all source documents used to complete the study forms (see section 10.1 above). A source document is defined as the first document on which study-related information is recorded. All data collection forms and source documents will be kept in locked files in a secure area, with access limited to study staff only.

Source documents will be kept in a locked file cabinets in the office. All locator information forms will be kept in locked files in a secure area separate from any other study document. In order to protect the participants confidentiality, under no circumstances will documents bearing participants names or other personal

identifiers be stored together with documents bearing the participants ID number.

The project will maintain a log or database containing the link between participant names and ID numbers. Written logs and/or database print outs will be stored in a secure location separate from participant files, with access limited to the Field Director and the Data Manager.

The project staff must adhere to the following standards of source documentation:

1. Although information may be copied from source documents onto other forms, or entered onto a computer database, all original source documents must be kept in the participant file.
2. The study participant whose information is contained in a source document must be identified by name or ID number, but not both, on the document.
3. All individuals who enter information onto source documents must be identified on the document, and must date all entries.
4. Change to entries on source documents must be initialled and dated by the individual making the revision. The individual's code should also be entered at the margin of the page.
5. Source documentation prepared by the project laboratory must be reviewed, signed and dated by designated technician (the tech's code number should be indicated at the margin).

## 11.0 STUDY TREATMENT

### 11.1.1 Drug supply, distribution and pharmacy

The study product and placebo are donated by 3-M Pharmaceuticals. MetroGel-Vaginal (0.75%) is an effective, well-tolerated local treatment for BV. Each gram of MetroGel-Vaginal contains 7.5 mg of metronidazole, 0.8 mg of methyparaben, 0.2 mg of propyl-paraben in an exclusive hydrogel vehicle consisting of purified water, propylene glycol, carbomer 934P, sodium hydroxide (to adjust pH), and edetate disodium. The gel is buffered to a normal pH of 4.0 and is free of mineral oil. Each applicatorful delivers about 5 grams of gel and contains approximately 37.5 mg of metronidazole in solution. The active product and placebo are identical with the exception that the placebo lacks metronidazole. The product should be stored at a temperature range of 15-30° C. An expiration date of at least two years will be ensured upon shipping the product from the U.S.

The receipt, dispensing and return of all study treatments will be documented by a designated project pharmacist, the project coordinator, on appropriate log forms.

Separate accountability records will be maintained for each shipment of drugs received by the project. A separate record will be maintained for all product supplies returned to the project unused by the participant. Assessment for compliance with product use will include return of the used product and applicators, checking the product number on returned product tube, and assessing amount of product used. These will be collected on the product dispensation and product monitoring forms that are completed at each visit.

All product inventory records will be stored in a locked file cabinet in a secure area of the project pharmacy, with access limited to the Field Director and the Project Coordinator.

### 11.1.2 Dosing

Each tube contains 70 g of metroGel-Vaginal. Study participants will be provided a single new product tube and a set of five new applicators at each visit. Women will use a new applicator each time the product is applied (dose 5 g per 5 ml applicator each night for five consecutive nights). The total amount of gel being used after each visit is therefore only about 25 g. Women will be instructed to bring back the tube so that the unused portion of the gel can be assessed.

Women will be instructed to use the product for 5 consecutive nights. The gel use should not be started during menses. If menses starts while the product is being applied, use should be discontinued and re-started when menses stops. If a woman forgets to insert the gel for any reason, she should apply it the following night until a total of five applications have been completed (i.e., all new applicators have been used). Women should be instructed not to clean or wash

the inside of the vagina until the following morning.

## 11.2 Adverse experiences

### 11.2.1 Summary

Intravaginal metronidazole gel is recommended by the Centers for Disease Control (CDC) for treatment of BV and no major risks have been reported when used in non-pregnant women. Minor complaints include yeast infection, vaginal irritation and rash. We will perform a wet mount at each visit (and at interim visit, if necessary) to monitor these infections and will provide treatment when clinically indicated. Information on use of the gel during pregnancy is limited. Therefore, the gel will be stopped if a woman becomes pregnant while using the gel. The dose of metronidazole intravaginal gel is very small compared to a usual oral metronidazole dose (about 188 mg intravaginal compared with 5000 mg oral). Additionally, systemic absorption of intravaginal gel was reported to be very low. Because some interactions have been reported between oral metronidazole use and alcohol, we will advise women not to drink alcohol while using the gel.

### 11.2.2 Monitoring of treatment side effects

Women will be closely monitored for acute and long-term side effects of metronidazole gel.

### 11.2.3 Management of side-effects

Women will be adequately counselled about side effects and instructed to report to the clinic if further assistance is needed (unscheduled visits). The project employs a full time clinical officer to provide clinical care to study participants. Specialized obstetric and adult medical care services are also available to the study participants.

### 11.2.4 Documentation and reporting of adverse experience

All adverse experiences (AEs) will be documented on the Adverse Experience case report form. All serious AEs (SAE) will be immediately reported to the principal investigators (on site and in the U.S.). See Appendix 4 for assessment of Adverse Experiences.

### 11.2.5 Non-study drug treatment

Studies from which women are recruited into the METRO trial provide at no cost all participating women multivitamin and iron supplements to safeguard against anemia. This commences at discharge from hospital after delivery and continues postnatally. All women with reactive syphilis serology will receive appropriate treatment. The children of these women will be assessed and provided treatment if clinically indicated.

## 12.0 STATISTICAL CONSIDERATIONS

### 12.1 General design issues

This is a randomized, double masked, controlled clinical trial to determine the effect of metronidazole intravaginal gel treatment on the incidence of BV among HIV positive and HIV negative women.

### 12.2 Endpoints

#### 12.2.1 Primary endpoints

- Incidence/Prevalence of BV at cross-sectional visits;
- Rate of conception and portion of pregnancies lost during the first 14 weeks of gestation;
- Incidence of adverse reactions to the product (portion of subjects having adverse reactions).

#### 12.2.2 Secondary endpoint

- Rates of participation in study, adherence to treatment, and subsequent dropout.

### 12.3 Randomization procedures

HIV positive and HIV negative women are randomized to receive either the active product (intravaginal metronidazole gel) or placebo gel. Five Study Clinics, including the QECH, are participating in this trial (more clinics could be added in the future). The allocation of study IDs for each clinic are shown below. Of the 1000 IDs assigned to each clinic, 500 will be for HIV positive clients and 500 will be for HIV negative clients. Of these 500 IDs for each of the HIV positive or HIV negative clients, half will be randomized to active product and the other half to placebo. The exact number of clients each clinic will enrol will depend on sample size (see Section 12.4.1).

| Clinic | Code | ID Range HIV -ve | ID Range HIV+ve |
|---------------|-------------|-------------------------|------------------------|
| QECH          | 1           | 11001-11500             | 12001-12500            |
| Limbe         | 2           | 21001-21500             | 22001-22500            |
| Cholomoni     | 3           | 31001-31500             | 32001-32500            |
| Zingwangwa    | 6           | 61001-61500             | 62100-62500            |
| Ndirande      | 7           | 71001-71500             | 72001-72500            |

#### 12.3.1 Instructions for using the allocation study ID's

##### By Whom

Study coordinator (as the rest of the study investigators and workers, the study coordinator is completely blinded about the treatment assignment).

Procedure

1. Assign these Lists to the five Study Clinics as shown in section 12.3. above
2. Each woman enrolling in the study will be sequentially assigned the next available ID in each clinic.

12.4 Sample size and analysis plan12.4.1 Sample size and power:

The following design specifications will apply: number of treatment groups: 2; follow-up period: approximately one year; hypotheses will be tested using a one-sided type 1 error of  $\alpha=0.05$ . Unless stated otherwise, powers are obtained based on Fisher's exact test for comparisons of proportions in two groups.

We will recruit 1664 women of whom 832 will be HIV infected and 832 will be uninfected. In each group of women, 416 will be randomized to treatment arm and 416 to placebo arm. Based on previous experience in Malawi, losses due to dropouts and non-compliance will be less than 10% per year. Thus at least 375 women in each arm will return to each study visit during the first year.

Primary endpoint: effect of treatment on BV incidence. Power estimates for this primary endpoint are shown in Tables 12.1. In previous studies from Malawi, cross sectional prevalence of BV among untreated women was 30% and that of any vaginal disturbance was 89%.

**Table 12.1. Estimated power for specific aim 1 (comparing BV at each visit during the first study year assuming at least 375 evaluable study subjects in each group).**

| Normative rate
in untreated women | Reduction from intervention |       |
|--------------------------------------|------------------------------------|-------|
|                                      | 33%                                | 50%   |
| 0.30                                 | .87                         | ~1.00 |
| 0.89                                 | ~1.00                       | ~1.00 |

Thus there will be **0.87** and almost **1.00** power to detect 33% reductions in cross sectional visit prevalence of BV (normative rate 0.30 in untreated subjects) and any vaginal flora disturbance (normative rate .89 in untreated subjects).

Primary endpoint: effect of treatment on rates of conception and early pregnancy loss. Previous reports suggest that 20%-30% of women without treatment will lose their first post-index pregnancy. Table 12.2. presents powers to detect 33% and 50% reductions in the rates of early gestational loss of this first post index pregnancy based on 300 evaluable subjects in each group (we have assumed that 80% of these women will become pregnant again). There is virtual certainty to detect 50% reductions if pregnancy loss of 30% occurs, and >90% reduction if the rate of pregnancy loss is 20%. For a 33% reduction, there is about 80% power if the rate of loss is high (30%) and limited power if the rate of pregnancy loss is low (20%).

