For some analyses we will pool repeated measurements from the same individual over multiple study visits. For example, occurrence of BV across all post-intervention study visits will be compared between study groups. For these analyses, generalized estimation equation models, which use an individual as cluster unit, will be fit to obtain robust covariance. For binary outcomes, a logit link will be used.

Data monitoring and reporting. This trial will be monitored by a Data and Safety Monitoring Board (DSMB). Formal interim analyses of efficacy of the intervention, based on the primary endpoints, will then be performed at approximately six month intervals during the projected study duration. Recommendations for early termination of positive or negative results will be guided by the symmetric group sequential O'Brien-Fleming Boundary (58). The O'Brien-Fleming design allows for early termination if extreme initial results are seen, while essentially allowing employment of the standard single stage one-sided 0.025-level test statistic at the final analysis if it is reached. This enables one to maintain the power of the single-stage design in the presence of interim monitoring without having to increase the maximum sample size. As has been the plan for other clinical trials conducted by our research team in Malawi, we will arrange for regular dissemination of information.

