#### 12.7 Data monitoring

This trial is monitored by a local Data and Safety Monitoring Board (DSMB). The members of the DSMB have no vested interest in this study. An initial administrative/safety analysis will be performed after the first three months of accrual. This will be followed by formal analyses of safety and efficacy of the intervention, based on the primary endpoints. Rates of accrual, retention, adherence and adverse events will be closely monitored and presented to the DSMB.

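### The plan sets the test level at one-sided 0.05, but its own final O'Brien-Fleming test and its power tables use one-sided 0.025

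*Protocol*

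**What the plan says.** The protocol file holds a research plan (section D.4) and a later manual of operations (section 12). Both contain the same sample-size paragraph.

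- **Test level (D.4, Sample size and power; 12.4.1).** "hypotheses will be tested using a one-sided type 1 error of" 0.05.
- **Power method (same paragraphs).** "powers are obtained based on Fisher's exact test for comparisons of proportions in two groups".
- **Group sizes (same paragraphs).** Within each HIV stratum "416 will be randomized to treatment arm and 416 to placebo arm". Because "losses due to dropouts and non-compliance will be less than 10% per year", the plan concludes that "at least 375 women in each arm will return to each study visit".
- **Final test (D.4, Data monitoring and reporting).** The O'Brien-Fleming design is described as "essentially allowing employment of the standard single stage one-sided 0.025-level test statistic at the final analysis". The boundary is called symmetric and covers stopping for positive or negative results.
- **Monitoring in the manual (12.7).** After a first administrative and safety analysis, "This will be followed by formal analyses of safety and efficacy of the intervention, based on the primary endpoints". No boundary or level is repeated there.

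No sentence in either part reconciles 0.05 with 0.025.

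**The concern.** A test level is the rule that decides whether a primary hypothesis is declared shown. Here two levels are given for the same hypotheses, both in section D.4. One-sided 0.05 corresponds to a critical value of z = 1.645, and one-sided 0.025 to z = 1.960. A result between them would be a success under the sample-size paragraph and a failure under the monitoring paragraph, and the choice could then be made after the data are seen.

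The power tables ought to show which level the designers used. If they were computed at 0.025 while the text announces 0.05, the announced test runs at twice the false-positive rate on which the tables rest, and the printed powers do not describe the announced test.

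**Working it through.** **Inputs**

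- Test: Fisher's exact test for two proportions (D.4, 12.4.1).
- Aim 1: 375 evaluable women per arm (416 × 0.9 = 374.4); BV prevalence 0.30 or any disturbance 0.89 in untreated women; reductions of 33% and 50% (Tables 11 and 12.1).
- Aim 2: 300 evaluable women per arm (375 × 0.8 = 300, using the plan's assumption that 80% become pregnant again); pregnancy loss 0.20 or 0.30; reductions of 33% and 50%. The printed powers are taken from Table 12 in D.4. The text of Table 12.2 as available shows no values, but its stated inputs are the same.
- Levels compared: one-sided 0.05 as stated, and one-sided 0.025 as in the monitoring paragraph.

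**Method.** For n women per arm, control rate p₁ and treated rate p₂ = p₁ × (1 − reduction), the exact power is

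Σ over (x₁, x₂) of Bin(x₁; n, p₁) × Bin(x₂; n, p₂),

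summed over the outcomes that the test rejects. With m = x₁ + x₂, it rejects when the hypergeometric tail P(X₂ ≤ x₂ | m) is at most the level. The 33% reduction was run as 0.33 and as 1/3, which gives the ranges below. As an example, for BV p₂ = 0.30 × 0.67 = 0.201, or 0.200 with 1/3.

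**Results**

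| Control rate, reduction, n per arm | Printed | At one-sided 0.025 | At one-sided 0.05 |
|---|---|---|---|
| BV 0.30, 33%, 375 | .87 | .865–.872 | .921–.926 |
| Loss 0.20, 33%, 300 | .54 | .543–.553 | .662–.671 |
| Loss 0.20, 50%, 300 | .91 | .920 | .957 |
| Loss 0.30, 33%, 300 | .78 | .775–.784 | .858–.865 |
| Loss 0.30, 50%, 300 | .99 | .992 | .997 |
| BV 0.30, 50%, 375 | ~1.00 | .998 | .999 |
| Any disturbance 0.89, 33%, 375 | ~1.00 | 1.000 | 1.000 |

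The last three rows sit near the ceiling and fit either level, so they carry no information here. The first four discriminate. At 0.025 each is within about one point of print. At 0.05, taking 33% as 0.33, the gaps are:

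- .921 − .87 = .051
- .662 − .54 = .122
- .957 − .91 = .047
- .858 − .78 = .078

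That is roughly 5 to 12 points. For the BV cell, a pooled z-test (.932–.937) and a continuity-corrected normal approximation (.921–.926) also miss .87 at one-sided 0.05, so the mismatch does not come from the choice of Fisher's test.

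The false-positive ratio between the two levels is 0.05 / 0.025 = 2.

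**The case against.** **The aim 2 cells have another reading.** The sentence before Table 12 could be taken to mean that 80% of the 300 women become pregnant, which leaves 300 × 0.8 = 240 per arm. Fisher's test at one-sided 0.05 with 240 gives .575, .911, .778 and .987 against the printed .54, .91, .78 and .99. Three of four agree to rounding. This stands as a reason not to rest the case on Table 12 alone. It does not rescue 0.05: the .54 cell still misses, 375 × 0.8 = 300 explains the printed group size, and the BV cell, which involves no pregnancy assumption, fits only 0.025.

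**Nothing is under-recruited.** This stands. At 0.05 the power exceeds the printed values, and at 0.025 it equals them.

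**Section 12.7 is only brief.** This also stands. A boundary not repeated in the manual is detail that D.4 supplies. It is a place to add a cross-reference, and not a second contradiction.

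**Stronger conclusions that a reader might draw.**

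- That harm could never be formally declared. The boundary in D.4 is symmetric and covers negative results, and the analysis sections promise confidence intervals.
- That a one-sided test cannot suit adverse reactions or conception. The plan says one-sided without giving a direction. A one-sided test for excess adverse reactions is a natural choice, and the direction for conception can be left to an analysis plan.
- That the overall error would be inflated by interim looks built for 0.025 followed by a final test at 0.05. No section plans that pairing, and the number of looks is not fixed.

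**Conclusion.** The contradiction holds. The sample-size paragraphs of D.4 and 12.4.1 say one-sided 0.05, and the monitoring paragraph of D.4 says one-sided 0.025 for the final test. The four informative power cells agree with 0.025 and lie 5 to 12 points below the power at 0.05. The 0.05 sentence is therefore the outlier. As written, a one-sided p-value between 0.025 and 0.05 has no defined outcome, and applying 0.05 would double the false-positive rate behind the tables.

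The conclusion assumes the plan's own test, rates and group sizes, with 300 per arm for aim 2. The direct conflict between the two stated levels does not depend on any calculation. The finding does not say that the sample size is too small: the plan itself already acknowledges limited power for a 33% reduction from a 20% loss rate, and this conflict does not worsen it.

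**What to change.** In D.4 (Sample size and power) and in 12.4.1, replace the one-sided type 1 error of 0.05 by a one-sided type 1 error of 0.025 (equivalent to two-sided 0.05). This agrees with the symmetric O'Brien-Fleming boundary already described in D.4. In 12.7, add a reference to that boundary for the formal efficacy analyses.

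The change takes one sentence in each of the three places and should be made before unblinding. The sample size of 1664 and all printed powers stay as they are. The only cost is giving up the more lenient 0.05 threshold. Making every endpoint formally two-sided would be a further design choice that this finding does not require.

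### The protocol states two final significance levels, one-sided 0.05 and one-sided 0.025, and its power tables reproduce at 0.025, not at the 0.05 stated beside them

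*Protocol*

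**What the plan says.** The sample-size paragraph appears twice in the Protocol file: in section D.4 of the research plan and in section 12.4.1 of the manual of operations. Both say "hypotheses will be tested using a one-sided type 1 error of" 0.05, and both say that, unless stated otherwise, "powers are obtained based on Fisher's exact test for comparisons of proportions in two groups".

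In each HIV group, "416 will be randomized to treatment arm and 416 to placebo arm". After losses the plan expects 375 per arm: "Thus at least 375 women in each arm will return to each study visit during the first year". For aim 1 the control rates come from earlier Malawi studies, where "cross sectional prevalence of BV among untreated women was 30% and that of any vaginal disturbance was 89"%. Table 11 (D.4) and Table 12.1 (manual) give power .87 for a 33% reduction from 0.30. For aim 2, Table 12 of D.4 uses 300 per group and gives .54 and .91 at a loss rate of 0.20, and .78 and .99 at 0.30, for reductions of 33% and 50%.

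The data-monitoring paragraph of D.4 adopts a symmetric O'Brien-Fleming boundary and describes it as "essentially allowing employment of the standard single stage one-sided 0.025-level test statistic at the final analysis if it is reached". It adds that this preserves the power of the single-stage design without a larger sample.

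Manual section 12.7, after an initial administrative and safety analysis, says: "This will be followed by formal analyses of safety and efficacy of the intervention, based on the primary endpoints". It names no level or boundary.

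**The concern.** The two statements in D.4 describe the same final test at different levels. The O'Brien-Fleming adjustment does not explain the gap: the monitoring text treats 0.025 as the ordinary single-stage level that interim looks leave almost untouched, not as 0.05 reduced to pay for those looks. So the single-stage design is 0.05 in one paragraph and 0.025 in another.

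At stake is the rule for declaring success on the primary endpoints. A one-sided p-value between 0.025 and 0.05 passes under the sample-size text and fails under the monitoring text. With both in the plan, the governing threshold could be settled after the results are known. The power tables show which level the design calculations used.

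**Working it through.** **Inputs, all from D.4 and 12.4.1.** One-sided Fisher's exact test with equal arms. Aim 1: 416 × 0.90 = 374.4, taken as 375 per arm, control rate 0.30. Aim 2: 0.80 × 375 = 300 per arm, control rates 0.20 and 0.30. The active rate is the control rate × (1 − reduction). For a 33% reduction, 0.30 × 0.67 = 0.201 and 0.20 × 0.67 = 0.134. Reading 33% as one third gives 0.200 and 0.133. For 50%, the active rates are 0.15 and 0.10.

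**Formula.** With x cases on placebo, y on active, t = x + y and n per arm, the one-sided Fisher p-value is p(x, y) = Σ over a ≥ x of C(n, a) C(n, t − a) / C(2n, t). Power is the sum over all (x, y) of Bin(x; n, placebo rate) × Bin(y; n, active rate), counting only pairs with p(x, y) ≤ α.

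**Reproducing the tables.** Where a range is shown, the first value uses 33% and the second one third.

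| n per arm | Rates | Printed | α = 0.025 one-sided | α = 0.05 one-sided |
|---|---|---|---|---|
| 375 | 0.30 vs 0.201 (0.200) | .87 | 0.865–0.872 | 0.921–0.926 |
| 300 | 0.20 vs 0.134 (0.133) | .54 | 0.543–0.553 | 0.662–0.671 |
| 300 | 0.20 vs 0.10 | .91 | 0.920 | 0.957 |
| 300 | 0.30 vs 0.201 (0.200) | .78 | 0.775–0.784 | 0.858–0.865 |
| 300 | 0.30 vs 0.15 | .99 | 0.992 | 0.997 |

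At 0.025 every cell is within about 1 point of print. At 0.05 the first four miss by about 5, 12 to 13, 5 and 8 points. The .99 cell and the ~1.00 cells of Table 11 do not discriminate, so the evidence rests on .87, .54, .78 and, a little less exactly, .91.

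**Is it the formula rather than the level?** For the first row at one-sided 0.05, the uncorrected normal, continuity-corrected and arcsine formulas give 0.932, 0.921 and 0.933. For the second row they give 0.700, 0.661 and 0.703. None approaches .87 or .54. Two-sided 0.05 gives the same powers as one-sided 0.025, so the authors may have computed at two-sided 0.05; the conclusion is the same.

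**Effect on a decision.** Take 112 of 375 placebo cases (112/375 = 0.299, close to the planned 0.30):

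| Active cases of 375 | Observed reduction | One-sided Fisher p | At 0.05 | At 0.025 |
|---|---|---|---|---|
| 87 | 1 − 87/112 = 22% | 0.0235 | success | success |
| 88 | 1 − 88/112 = 21% | 0.029 | success | failure |
| 89 | 1 − 89/112 = 21% | 0.035 | success | failure |
| 90 | 1 − 90/112 = 20% | 0.042 | success | failure |

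**False-positive rate.** The nominal ratio is 0.05 / 0.025 = 2. Fisher's test is conservative: its actual size at the planned group sizes and control rates is about 4.1% to 4.3% at nominal 0.05 and about 2.0% to 2.1% at nominal 0.025. The ratio is still about two.

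**The case against.** The strongest reply is that no sentence says which level governs. If 0.05 was intended, then the monitoring sentence and the tables are what need correcting, and the printed powers are merely conservative, because every cell is as high or higher at 0.05. This stands. The documents show an unreconciled level; that 0.025 was the design level is an inference, though two independent parts of the plan support it.

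It can also be said that the verdict changes only in a narrow band: three counts in the example above. That is true and limits the practical reach. But a success threshold is fixed in advance precisely to settle results in that band.

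A reader might go further and infer that, because 12.7 plans formal efficacy analyses without naming a boundary, the manual permits repeated unadjusted tests at 0.05, with a much inflated error rate. The documents do not support this. Section 12.7 states no level, no number of efficacy looks and no instruction to test unadjusted. D.4 names an O'Brien-Fleming boundary, and nothing in 12.7 withdraws it. Such detail may also sit in a separate analysis or monitoring plan.

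The cells of the manual's Table 12.2 are absent from the text available here, so the aim 2 check rests on Table 12 of D.4.

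**Conclusion.** The point holds as a contradiction supported by arithmetic. The plan names two final levels, and the powers printed with the 0.05 statement were not computed at 0.05. They fit one-sided 0.025 (two-sided 0.05), the level that the monitoring text of D.4 also names. Taking 0.05 as simply an error would go further than the documents do; they leave the level unresolved, with the weight of evidence towards 0.025.

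Nor does the mismatch make the trial underpowered. On the planned inputs, the powers are those printed at 0.025 and higher at 0.05. The consequences are an undefined success threshold for one-sided p-values between 0.025 and 0.05 and, if 0.05 is applied, a nominal false-positive rate per test twice the one the powers assume. The result rests on the plan's own rates, group sizes and choice of test. The 112/375 placebo count is an illustration at about the planned rate.

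**What to change.** State one final level in the sample-size paragraphs of D.4 and 12.4.1: one-sided 0.025, equivalent to two-sided 0.05. The tables and the D.4 monitoring text already support it. Leave the sample size and the printed powers unchanged. Wherever interim efficacy analyses are described, including 12.7, refer to the D.4 O'Brien-Fleming boundary at that same level.

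The cost is wording only. The final threshold becomes the stricter of the two now stated, at the power the tables already print. If the sponsor did intend one-sided 0.05, the monitoring sentence in D.4, its boundary and the power tables would all have to be restated to match, with powers of about 0.92–0.93, 0.66–0.67, 0.96, 0.86–0.87 and 0.997. Either way, the choice should be recorded before any unblinded efficacy comparison.
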